### Control group

TAU for anxiety in people with mild intellectual disability consists of a single component-adapted psychological treatment to develop coping skills. TAU provides support with identifying and linking thoughts with emotions and developing problem-solving skills. These will be provided by community multidisciplinary team members and will be delivered once a week for up to 12 weeks.

### Training of professionals in delivery of anxiety management interventions

Clinicians across all four sites within the NHS trust will receive standardised training on the delivery of the MCAMP-ID programme (intervention group) and a separate training session for single-component therapy (control group). Training will be delivered jointly by people with lived experience (PwLE) and clinical psychologists who are part of the research study team. The training will include using the easy-to-read materials to ensure reasonable adjustments and accessibility of treatment intervention.

### Quantitative measures

Clinical outcome measures will be completed in three stages: baseline, at 12 weeks and 20 weeks (8 weeks post-completion) of the programme (either face to face, telephone or via video link).

### Primary outcome measure

#### Glasgow Anxiety Scale

The GAS-ID is a 27-item self-rating scale for people with intellectual disabilities which is designed to identify cognitive, behavioural and somatic symptoms, which co-present with anxiety disorders.^25^ The GAS-ID is chosen because it provides a robust and validated assessment of a person’s level of anxiety which has been specifically designed for people with intellectual disability.

### Secondary outcome measures

#### Hospital Anxiety and Depression Scale

The HADS is a 14-item interview questionnaire that measures depression, anxiety and severity of the emotional disorder.^26^ The HADS is an effective validated measure that has been chosen to identify any correlation between levels of anxiety and depression in people with intellectual disability.

#### Client Satisfaction Questionnaire

The CSQ-8 is an eight-item measure of client satisfaction eliciting the client’s perception of the mental health services and intervention rated on a 4-point Likert scale.^28^ To understand patients, families and carers on the development, experience of going through the intervention, and acceptability of the intervention and the manual, the CSQ-8 will be completed at end of intervention (12 weeks).

#### WHO Quality of Life Measure

The WHOQOL-8 is an eight-item quality of life measure covering four domains of the original 26-item version.^27^ To measure quality of life, we will use an adapted version of the WHOQOL. This consists of eight questions rated on a 4-point Likert scale.

#### Client Service Receipt Inventory

The Client Service Receipt Inventory (CSRI) is a questionnaire used to estimate service utilisation and will be used to evaluate the cost and use of health resources and services by service users with psychiatric problems.^31^ A modified version of the CSRI will be tailored to the specific context in collaboration with the PPI group and used to capture health service usage, baseline clinical characteristics of participants and adherence to the study.

### Qualitative approach

On completion of the intervention, participants will be invited to attend a focus group or individual interview facilitated by PwLE and a member of the research team. Semistructured interview questions will be used to understand participants’ thoughts and feelings of the anxiety management intervention. All interviews will be audio-recorded and transcribed verbatim. Thematic analysis process described by Braun and Clarke^32^ will be used to analyse the transcripts.

### Quantitative analysis

Data will be analysed using the computer software program SPSS (V.28). The descriptive analysis will focus principally on recruitment rates, characteristics of participants and the function of the programme manuals. The primary outcomes (mean scores and CIs) will be reported at baseline, 12 weeks and 20 weeks (8 weeks post-completion) for both comparative arms. The variability of the primary outcome measure will be used to inform the power calculation and sample size for the definitive RCT. Additionally, we will complete analyses of treatment preference and number of sessions received.

A descriptive analysis of total NHS costs and individual resource use components will be completed.

### Criteria for progression to full RCT

We will consider progressing to a full RCT, if we are able to recruit and retain participants. Therefore, feasibility of recruitment will be a key aspect of this feasibility study. A Stop/Go process will be used to ascertain the percentage of participants recruited to the trial. Go: 100% recruited and at least 80% of eligible participants retained. Review: 50–79% of eligible participants recruited; Stop: <50% participants recruited. With the retention rate of 80%, a sample size of 60 will allow these outcomes to be estimated with an accuracy of ±11%.

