### Sample size

A total of 60 adults with intellectual disabilities will be invited to participate in the study. Sample sizes of between 50 and 60 are considered large enough to allow sufficient power to evaluate feasibility of a definitive RCT.^30^

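### The Stop/Go rule is not exhaustive: recruiting 48–59 of 60, or all 60 with under 80% retained, falls in no category, and the bases of its percentages are unstated or differ

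*Protocol article*

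**What the plan says.** The rule is in the protocol article under Criteria for progression to full RCT. It opens by resting progression on two things: "We will consider progressing to a full RCT, if we are able to recruit and retain participants". It then sets three categories: "Go: 100% recruited and at least 80% of eligible participants retained. Review: 50–79% of eligible participants recruited; Stop: <50% participants recruited".

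The paragraph closes with a precision statement: "With the retention rate of 80%, a sample size of 60 will allow these outcomes to be estimated with an accuracy of ±11" percent.

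Two other places bear on the base of 60. Study design gives 30 participants to each arm, and Sample size says: "A total of 60 adults with intellectual disabilities will be invited to participate in the study". Nothing elsewhere in the article adds a band or says what each percentage is taken over.

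**The concern.** A Stop/Go rule should return one category for every result the trial can produce. This one has thresholds for all three categories, but they do not meet. Review ends at 79% and Go starts at 100%. Retention is half of the stated basis for progression, yet it has no Review or Stop band, so no amount of drop-out can by itself lead to Stop. The wording of the base also changes from clause to clause.

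Whether a definitive trial is feasible is a stated aim of the study, and this is the only progression rule in the article. Where the rule gives no category, the team has to choose one after seeing the data, which is what fixing a rule in advance is meant to avoid.

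**Working it through.** **Inputs.** Go, Review and Stop thresholds, the 80% retention rate and the ±11% come from Criteria for progression to full RCT. The target of 60 comes from Study design (2 × 30) and Sample size. The confidence level is not stated; 95% two-sided is assumed.

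**1. The plan's own figure.** For 48 of 60 (80%):

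- Exact (Clopper-Pearson) interval: 67.7% to 89.2%, half-width (89.2 − 67.7)/2 ≈ 10.8%.
- Wald with continuity correction: 1.96 × √(0.8 × 0.2/60) + 1/(2 × 60) = 0.1012 + 0.0083 = 0.1095, or 11.0%.
- Plain Wald: 10.1%.

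The ±11% reproduces with the exact or continuity-corrected interval and is not in question.

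**2. Recruitment bands, base 60.**

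| Recruited | Percent of 60 | Category |
|---|---|---|
| 0–29 | 0–48.3 | Stop |
| 30–47 | 50.0–78.3 | Review |
| 48–59 | 80.0–98.3 | none |
| 60 | 100 | Go, if retention is at least 80% |

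A trial that enrols 59 of 60 gets no category, while one that enrols 47 gets Review.

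**3. Retention at full recruitment.** With 60 recruited and retention counted over those enrolled, Go needs 0.80 × 60 = 48 retained. With 47 or fewer, Go fails. Review and Stop fail too, because each depends only on recruitment and recruitment is 100%. With X ~ Binomial(60, p), the chance of no category is 1 − P(X ≥ 48):

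| True retention p | P(X ≥ 48) | Chance of no category |
|---|---|---|
| 0.75 | 0.232 | 0.768 |
| 0.80 (the plan's rate) | 0.576 | 0.424 |
| 0.85 | 0.894 | 0.106 |
| 0.90 | 0.994 | 0.006 |

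Only the 0.80 row uses a rate from the article; the others show the range. All rows are conditional on exactly 60 recruited.

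**4. Denominators.** Go recruitment names no base, Go retention and Review recruitment name eligible participants, and Stop names no base. The eligible pools below are assumed for illustration.

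- *Recruitment all on the target of 60:* the categories cannot overlap, and the gaps in steps 2 and 3 stand.
- *Go recruitment on the target, Go retention on those enrolled, Review on the eligible pool:* 60 recruited and 50 retained gives 60/60 = 100% and 50/60 = 83%, so Go. With 100 eligible, 60/100 = 60%, so also Review. With 60 recruited, the Review condition is met for pools from 76 (60/76 = 78.9%) to 120 (60/120 = 50%).
- *Go retention literally on the eligible pool:* at least 80% of eligible people retained implies at least 80% of them recruited, so Go cannot overlap Review, or Stop on that base.

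**The case against.** The strongest reply is that the bands guide a judgement. The article says only that progression will be considered, recruitment and outcomes are to be reported descriptively in any case, and an unclassified result would most naturally be treated as Review. No participant's care and no estimate depends on the rule. This stands as a limit on the harm. It does not repair the rule, because nothing in the text sends an unclassified result to Review.

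Three stronger readings are tempting, and the article does not support them.

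- A reader might infer that any retention below 80% is unclassified. It is not. With 30–47 recruited the result is Review, and with fewer than 30 it is Stop, whatever the retention. The retention gap arises at full recruitment.
- A reader might infer that one result can be both Go and Stop. That needs Go recruitment on the target, retention on those enrolled (against the wording), Stop on the eligible pool (which the Stop clause does not name) and, with 60 recruited, at least 121 eligible people (60/121 = 49.6%). The article gives no pool size.
- A reader might infer that unclassified recruitment is likely because 12 of the 61 counts from 0 to 60 have no category. Those counts are not equally likely, and the article gives no eligible pool or consent rate from which to judge.

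It could also be said that an article condenses a fuller protocol. That would excuse missing detail, but here all three thresholds are printed and do not fit together.

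**Conclusion.** The rule is wrong as written. On the target of 60, recruitment of 48–59 has no category, and neither does full recruitment with 47 or fewer retained. The recruitment gap needs no assumption beyond a single base for all three bands: 80–99% is uncovered whichever base that is. At full recruitment, and at the plan's own 80% retention, the chance of no verdict is about 42%. That figure assumes retention counted over those enrolled and independent drop-out.

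The bases need stating in any case. The possible overlap of Go with Review is conditional on a mixed reading and on an unknown eligible pool, so it is a reason to fix the wording and not a demonstrated contradiction. The same mixed reading would place some of the otherwise unclassified results in Review, depending on the pool. How likely 48–59 recruited is cannot be shown from the article.

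**What to change.** Reword the paragraph as follows.

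- State one denominator for recruitment, for example the target of 60, and one for retention, namely participants enrolled.
- Make the recruitment bands contiguous. The smallest repair that keeps the sponsor's Go at 100% is Review 50–99% and Stop below 50%. Lowering Go is a separate choice for the study team and is not needed to close the gap.
- Send full recruitment with retention below 80% to Review at least. Whether retention also has a Stop cut-off, and where, is for the study team to decide.
- State that the overall verdict is the worse of the two criteria.

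The cost is one paragraph and an amendment, which under Ethics and dissemination needs Health Research Authority approval before it takes effect. No new data are needed. Since recruitment has started, the wording should be settled before recruitment and retention results are reviewed.

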### Reporting

The Consolidated Standards of Reporting Trials (CONSORT) extension for pilot and feasibility studies will be used to guide reporting of the study results and monitor the flow of participants recruited to the study.^33^
Figure 1 is the template for the CONSORT study flow diagram, giving an overview of the study design and planned process of participant recruitment.

**Figure 1 F1:**
[figure not shown]
Template for the study flow diagram.

### Patient and public involvement

People with intellectual disability have been involved in co-producing and developing the multicomponent anxiety management programme manuals. They will be part of the PwLE group and will continue to play an active role in the feasibility trial by co-developing and designing resources and information leaflets, developing and delivering staff training, co-facilitating focus groups and analysing qualitative data. Additionally, the PwLE group are independent from the sponsor and will chair the trial committee. A participation and engagement practitioner will provide support to the PwLE group throughout the trial, to ensure people are fully supported to engage in all aspects of the study.

## Ethics and dissemination

The study received approval from the Research Ethics Committee and Health Research Authority (23/EM/0044) through the Integrated Research Application System (IRAS ID: 315557) in March 2023. Any amendments to the protocol or procedures will require approval from the Health Research Authority before any changes are made. Participants will be required to provide informed consent before taking part (online supplemental material).

The results of the study will be published in peer-reviewed journals with the findings disseminated at conferences, professional networks, social media and family carer forums. A short film will be made with the PPI group detailing the value of co-production with people who have a lived experience of anxiety in developing psychological interventions.
